**Additional question regarding self-harm and suicidality**

| Is your child currently having thoughts about hurting themself or ending their life? | Yes/No |
| --- | --- |

About your child’s health

| 1. | Does your child have an eating disorder diagnosis? | Yes/No |
| --- | --- | --- |
|  | *If yes to 1 – please specify:* |  |
|  | *Which eating disorder your child has* | Anorexia Nervosa  Bulimia Nervosa  Binge Eating Disorder  Other Specified Feeding or Eating Disorder (OSFED) |
|  | *How old your child was when they were diagnosed with an eating disorder* |  |
|  | *Who diagnosed your child with an eating disorder (e.g., CAMHS, private treatment provider)* |  |
| 2. | Is your child currently receiving any psychological treatment for their eating disorder (e.g., family-based therapy, cognitive behavioural therapy, counselling etc.)? | Yes/No |
|  | *If yes to 3 – please specify:* |  |
|  | *What treatment your child is currently receiving (e.g., family-based therapy, cognitive behavioural therapy, counselling etc.)* |  |
|  | *The length and duration of the treatment (i.e., the number of sessions your child has received/will receive in total)* |  |
|  | *When you are due to finish this treatment (if known)* |  |
|  | *Where your child is receiving this treatment (e.g., CAMHS, private treatment provider)* |  |
| 3. | Is your child currently prescribed any medication for mental health difficulties (e.g., sertraline, fluoxetine)? | Yes/No |
|  | *If yes to 3 – please specify:* |  |
|  | *What medication your child has been prescribed* |  |
|  | *How long your child has been taking this medication at the current dosage* |  |
| 4. | Is your child currently on the waitlist for treatment for their eating disorder? | Yes/No |
|  | *If yes to 4 – please specify:* |  |
|  | *What treatment your child is waiting to receive (e.g., CBT, counselling, medication, not known)* |  |
|  | *Where your child is waiting for treatment (e.g., CAMHS, private treatment provider)* |  |
| 5. | Has your child previously received treatment for their eating disorder? | Yes/No |
|  | *If yes to 5 – please specify:* |  |
|  | *What treatment your child received (e.g., family-based therapy, cognitive behavioural therapy, counselling etc.)* |  |
|  | *The length and duration of the treatment (i.e., if a psychological therapy, the number of sessions your child received an over what time period or if medication, what medication and for how long were they taking this medication)* |  |
|  | *How old your child was when they received this treatment* |  |
|  | *Where your child received this treatment (e.g., CAMHS, private treatment provider)* |  |
| 6. | Has your child received a diagnosis for any other mental health condition? | Yes/No |
|  | *If yes to 6 – please specify*  What other mental health condition(s) your child has |  |

Other

| Is there any other information that you think is relevant that we haven’t asked? |  |
| --- | --- |

| How did you hear about this study? |  |
| --- | --- |

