**Study summary**

| Title | Short Psychological Intervention for Children and adolescents with Eating disorders (SPICE) study |
| --- | --- |
| Sponsor name | UCL Great Ormond Street Institute of Child Health |
| Primary objective | To evaluate the feasibility, acceptability and preliminary effectiveness of a guided self-help (GSH) intervention for children and young people (CYP) with eating disorders |
| Study design | Case series |
| Study endpoints | The final follow-up measurement (4 weeks post-intervention) for the final participant |
| Sample size (maximum) | Aim to recruit 10 CYP and their parents/carers |
| Summary of eligibility criteria | CYP  *Inclusion criteria:*   - Aged 8-19 years - Has a threshold or sub-threshold eating disorder (anorexia nervosa, bulimia nervosa, binge eating disorder, other specified feeding and eating disorder [OSFED]) which impairs their psychosocial functioning - UK resident - Has a parent/carer willing to take part in the study   *Exclusion criteria:*   - Does not speak/understand English sufficiently to access the measures and intervention materials - Has an intellectual disability at a level meaning that they cannot access the measures and intervention materials - Acute risk not considered suitable for the study due to the clinical need for immediate and/or specialist intervention (e.g., rapid weight loss, very low mood, high medical or psychiatric risk, acute suicidality, recurrent or potentially life limiting self-harm and/or significant safeguarding concerns) - Unstable psychotropic medication dosage - Receiving other overlapping psychological support - Does not have access to a telephone/computer which can be used for the assessment and guidance sessions   Parents/carers  *Inclusion criteria:*   - Parent/legal guardian of the CYP - UK resident   *Exclusion criteria:*   - Does not speak/understand English sufficiently to access the measures and intervention materials - Has an intellectual disability at a level meaning that they cannot access the measures and intervention materials |
| Intervention | CBT-based Self-help with 8 guidance sessions over 8 weeks |
| Procedures: Screening & enrolment | Families at specialist eating disorder services will be approached by a member of their clinical care team, and eligibility will be determined by a screening questionnaire and an eating disorder questionnaire (Eating Disorder Examination Questionnaire [EDE-Q]) |

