**Eligibility criteria**

### Children and young people

Inclusion criteria

The inclusion criteria for CYP:

1. Aged 8-19 years
2. Has a threshold or sub-threshold eating disorder (anorexia nervosa, bulimia nervosa, binge eating disorder and otherwise specified feeding and eating disorder [OSFED]) which impairs their psychosocial functioning
3. Is a UK resident
4. Have a parent/carer who is also willing to take part in the study

Exclusion criteria

The exclusion criteria for CYP:

1. Does not speak/understand English sufficiently well to access the measures and intervention materials. This is primarily due to limited funding capacities for interpreters
2. Has an intellectual disability at a level meaning that they cannot access the measures and/or intervention. This will not be defined by IQ, but by clinical judgement. CYP will not be excluded because of the presence of intellectual disability per se, but because of being unable to access the materials. Ability to participate may be different for younger children who are less able, whose parents complete the materials, compared to older children who need to complete the materials themselves. If the intellectual disability is identified during the initial assessment (through clinical judgement), young people will be referred to other more appropriate services as necessary (with agreement of the family)
3. Questionnaire indicates acute risk not considered suitable for the trial due to the clinical need for immediate and/or specialist intervention, e.g., rapid weight loss, very low mood, high medical or psychiatric risk, acute suicidality, recurrent or potentially life limiting self-harm and/or significant safeguarding concerns (i.e., if the child has a child protection plan and/or is on the child protection register, and/or the research team consider the child to be suffering, or likely to suffer, significant harm)
4. If they have been prescribed psychotropic medication, the dosage must have been stable for the past two months
5. Currently receiving other overlapping psychological support/interventions
6. Does not have access to a telephone or laptop/computer which can be used for the interviews and guidance sessions

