### Screening and eligibility assessment

Once families have been recruited through one of the recruitment sites, and have completed the study consent/assent forms, their eligibility for the research will be confirmed.

Families who consent/assent to participate in the study will be asked to complete a short screening questionnaire to determine their eligibility for participation (see [Appendix 1](#Appendix1)). This will include demographic information about the CYP and their parent(s)/carer(s), confirmation of UK residency, information about prescribed psychotropic medication of the CYP, current/previous psychological support received by the CYP, brief questions to determine if the CYP is experiencing possible symptoms of eating disorders that impair their functioning and a question around current self-harm and suicidality. This questionnaire can be completed online or via telephone with the study researcher. It is expected that this questionnaire will take approximately 15 minutes to complete. If families are not eligible for the study, the study researcher will contact the family to explain why they are not eligible for the research, and signpost them to relevant support, as necessary. If the screening questionnaire indicates that the family meet the eligibility criteria, they will be invited to enrol in the study.

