### Procedure once participants are enrolled

Once participants are enrolled into the study, CYP and their parents/carers will be invited to complete the baseline measures, including a battery of questionnaires, including the self-report of the Eating Disorder Examination Questionnaire [EDE-Q] and the parent-report of Eating Disorder Examination Questionnaire [PEDE-Q]). This is to confirm that the intervention is appropriate (i.e., that the CYP has impairing symptoms of eating disorders and an absence of significant risk as detailed in the inclusion/exclusion criteria). Families may also be asked to complete the online Development and Wellbeing Assessment (DAWBA) to enable an understanding of comorbid diagnoses. Note – the DAWBA will be piloted with families in the first instance. If the family have already completed the DAWBA during their assessment with the eating disorder service, this data will be accessed to prevent duplication of measures. Following the pilot, it may be decided to no longer use the DAWBA, and families will be asked to complete the Strengths and Difficulties Questionnaire (SDQ) at baseline instead.

Questionnaires will be sent to families to complete online (or over the telephone if preferred). The questionnaires will cover some additional demographic information about the family ([Appendix 2](#Appendix2)), brief questions about the CYP’s eating disorder symptoms and how they impair their functioning, and symptoms of anxiety and depression. They will also be asked to report on the CYP’s current weight and height. It is expected that these questionnaires will take approximately 15 minutes to complete. Families may also complete the DAWBA online (or over the telephone with a researcher if preferred) which will take around 45 minutes to complete.

Families will then be invited to attend a feedback appointment where the study researcher will feed back the information obtained from the questionnaires, and to discuss next steps regarding the intervention. This feedback appointment is likely to last around 30 minutes. The family will be given a report summarising the outcomes of the questionnaires and the next steps for treatment. The family’s GP and other teams involved in their care (e.g., eating disorder service) will also be sent a copy of this report to inform them about the family’s participation in the study.

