**Additional question regarding self-harm and suicidality**

| Are you currently having thoughts about hurting yourself or ending your life? | Yes/No |
| --- | --- |

About your health

| 1. | Do you have an eating disorder diagnosis? | Yes/No |
| --- | --- | --- |
|  | *If yes to 1 – please specify:* |  |
|  | *Which eating disorder you have* | Avoidant/Restrictive Food Intake Disorder (ARFID)  Anorexia Nervosa  Bulimia Nervosa  Binge Eating Disorder  Other Specified Feeding or Eating Disorder (OSFED) |
|  | *How old were you when you were diagnosed with an eating disorder* |  |
|  | *Who diagnosed you with an eating disorder (e.g., CAMHS, private treatment provider)* |  |
| 2. | Are you currently receiving any psychological treatment for your eating disorder (e.g., family-based therapy, cognitive behavioural therapy, counselling etc.)? | Yes/No |
|  | *If yes to 3 – please specify:* |  |
|  | *What treatment you are currently receiving (e.g., family based therapy, cognitive behavioural therapy, counselling etc.)* |  |
|  | *The length and duration of the treatment (i.e., the number of sessions you have received/will receive in total)* |  |
|  | *When you are due to finish this treatment (if known)* |  |
|  | *Where you are receiving this treatment (e.g., CAMHS, private treatment provider)* |  |
| 3. | Are you currently prescribed any medication for mental health difficulties (e.g., sertraline, fluoxetine)? | Yes/No |
|  | *If yes to 3 – please specify:* |  |
|  | *What medication you have been prescribed* |  |
|  | *How long you have been taking this medication at the current dosage* |  |
| 4. | Are you currently on the waitlist for treatment for an eating disorder? | Yes/No |
|  | *If yes to 4 – please specify:* |  |
|  | *What treatment you are waiting to receive (e.g., CBT, counselling, medication, not known)* |  |
|  | *Where you are waiting for treatment (e.g., CAMHS, private treatment provider)* |  |
| 5. | Have you previously received treatment for an eating disorder? | Yes/No |
|  | *If yes to 5 – please specify:* |  |
|  | *What treatment you received (e.g., family based therapy, cognitive behavioural therapy, counselling etc.)* |  |
|  | *The length and duration of the treatment (i.e., if a psychological therapy, the number of sessions you received and over what time period or if medication, what medication and for how long were you taking this medication)* |  |
|  | *How old you were when you received this treatment* |  |

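### The only self-harm item on the three screening forms asks about current thoughts, so a No cannot show that the self-harm behaviour named in exclusion 3 is absent

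*Protocol*

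**What the plan says.** The Protocol's eligibility section makes the questionnaire the trigger for CYP exclusion criterion 3: "Questionnaire indicates acute risk not considered suitable for the trial due to the clinical need for immediate and/or specialist intervention". The examples under that criterion include "acute suicidality, recurrent or potentially life limiting self-harm and/or significant safeguarding concerns". The Study summary repeats the examples and states that "eligibility will be determined by a screening questionnaire and an eating disorder questionnaire".

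Under Screening and eligibility assessment, the screening questionnaire is said to include "a question around current self-harm and suicidality". The Measures section describes it more loosely, as a question on current risk. The step to enrolment then follows from the form: "If the screening questionnaire indicates that the family meet the eligibility criteria, they will be invited to enrol in the study".

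The item itself is in Appendix 1. On the parent/carer form (1a) it is "Is your child currently having thoughts about hurting themself or ending their life". On the forms for CYP over 16 (1b) and under 16 (1c) it is "Are you currently having thoughts about hurting yourself or ending your life". Each is a single Yes/No question.

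After enrolment, the baseline measures are meant to confirm that the CYP has impairing symptoms and "an absence of significant risk as detailed in the inclusion/exclusion criteria".

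**The concern.** Exclusion 3 names self-harm that is recurrent or of a certain severity. That is behaviour with a history, and the criterion lists it separately from suicidality. The form asks only about a present state of mind. Acts, and their repetition, cannot be read from one question on current thoughts. A young person who self-harms but does not regard themselves as currently having such thoughts can truthfully answer No.

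What is at stake is whether a safety exclusion can be applied from its own stated trigger. The participants are aged 8 to 19. They receive self-help with guidance by videocall or telephone, in a form the Protocol says has not yet been evaluated in this group (Novel intervention). Appendix 5 says the research team does not hold clinical responsibility for the family. The screening form is the only enquiry about self-harm that the Protocol describes before enrolment.

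**Working it through.** No arithmetic applies beyond a count. The check compares the criterion with the forms, then looks for any other stated enquiry about self-harm acts.

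**Step 1. Criterion, description and item**

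| Place in the Protocol | Acts of self-harm | Recurrence or severity | Current thoughts |
| --- | --- | --- | --- |
| CYP exclusion criterion 3 | yes | yes | covered under suicidality |
| Screening and eligibility assessment (description of the item) | yes, current | no | covered under suicidality |
| Appendix 1a, parent/carer | no | no | yes |
| Appendix 1b, CYP over 16 | no | no | yes |
| Appendix 1c, CYP under 16 | no | no | yes |

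Forms with a self-harm or suicidality item: 3 of 3. Forms whose item is confined to current thoughts: 3 of 3. Forms that ask about self-harm behaviour or its recurrence: 0 of 3.

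**Step 2. Other content of the forms.** The ChEDE-Q8, the adapted SDQ impact questions and the questions on diagnoses, treatment and medication do not ask about self-harm. Forms 1a and 1b end with an open question inviting other relevant information; form 1c has none. An unprompted free-text box is not an enquiry about self-harm.

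**Step 3. Measures after screening.** The Study summary also names the EDE-Q as deciding eligibility. The Protocol describes it as covering eating disorder attitudes and behaviours. The PEDE-Q, CIA, RCADS and SDQ are likewise not described as asking about self-harm acts. The DAWBA may be used and may be dropped after piloting. Whether it contains such an item cannot be settled from the document, but it comes after enrolment in any case.

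**Step 4. Contacts with staff.** Appendix 5, sections 4.2 and 4.4, says that risk questions are not asked routinely in structured contacts or in guidance sessions. The prompt sheet in Appendix 5a does separate thoughts from actions and asks about both, but it is used once a risk has been disclosed. The Risk management section arranges further assessment at screening only when the questionnaire has identified risk. A No opens neither route.

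**Result.** On the procedures as described, nothing before enrolment asks about self-harm acts, and nothing after enrolment is stated to do so as routine.

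**The case against.** Four points on the other side deserve weight.

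- **Currently need not mean today.** Elsewhere on forms 1a and 1b the word describes ongoing status, such as treatment being received or medication prescribed. Read that way, many young people with recurrent self-harm would answer Yes. This stands. It narrows the route to a truthful No but does not close it.
- **There are other safeguards.** Families are approached by their own clinical care team at a specialist service. The item appears on both the parent and the CYP forms. Baseline measures and a feedback appointment follow, a report goes to the GP and other teams involved, and significant risk found later leads to withdrawal. This also stands as mitigation. However, the clinical team is given no stated task of checking exclusion 3, both informants get the same thoughts-only item, and none of the later steps is described as asking about acts.
- **The descriptions are loose.** The screening section speaks of a question around the topic, and the form is a brief first screen of about 15 minutes. On its own, that sentence is weak evidence of a contradiction. The main mismatch is between the criterion, which rests on what the questionnaire indicates, and the item.
- **The exclusion concerns acute risk, with self-harm as one example.** True, but the example is named, and the form gives no means of detecting it.

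A reader might go further and infer that young people who self-harm will be enrolled with their risk status recorded as clear, or might put a number on how many. The documents support neither. No section says that a No records risk as clear, and no figure is given for how common the excluded kind of self-harm is or how often it occurs without current thoughts.

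**Conclusion.** The mismatch is real and should be corrected. As written, the forms cannot establish that the behavioural part of exclusion 3 is absent, and the item asks for less than the Protocol's own description of it implies. The size is the count above: all 3 forms ask about thoughts and none asks about acts or recurrence. This shows a possible route to enrolment past a stated safety exclusion, not a certain or frequent one.

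The conclusion assumes that the appendix forms are used as printed and that the measures contain no self-harm item beyond what the Protocol describes. If a baseline instrument does contain one, the gap after enrolment would be smaller, but the gap at screening would remain. The point is limited to what a No can show; it does not concern what should follow a Yes.

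**What to change.** Reconcile CYP exclusion criterion 3, the description under Screening and eligibility assessment, and Appendices 1a, 1b and 1c. Keep the thoughts item on each form and add a brief item on self-harm behaviour, including whether it is recurrent, so that the form can trigger the exclusion as stated. Then describe the items in the screening section as they appear on the forms.

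The exact wording, including wording suited to the youngest children completing form 1c, the lookback period and the judgement of answers stay with the study team and supervisors. No clinical threshold is proposed here.

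The cost is a short amendment to three forms and one sentence of the Protocol, plus slightly more time for respondents.

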**Child Eating Disorder Examination Questionnaire (ChEDE-Q8; Kliem et al., 2017)**

| These questions are about the past two weeks only (14 days).  Please read each question carefully and circle the response for each question. | | Scoring | | | | | | |
| --- | --- | --- | --- | --- | --- | --- | --- | --- |
| On how many days of the past 14 days… | | No days | 1-2 days | 3-6 days | 7 days | 8-10 days | 12-13 days | Every day |
| Restraint over eating | …have you been trying to cut down on food to control your weight or shape? |  |  |  |  |  |  |  |
| Food avoidance | …have you tried not to eat any foods you like to control your weight and shape? |  |  |  |  |  |  |  |
| Preoccupation with food | …has thinking about food or calories made it much harder to concentrate on things you are interested  in; for example, reading, watching tv, or doing your homework? |  |  |  |  |  |  |  |
| Feelings of fatness | …have you felt fat? |  |  |  |  |  |  |  |
| Desire to lose weight | …have you had a very strong wish to lose weight? |  |  |  |  |  |  |  |
| Guilt about eating | Over the past 2 weeks/14 days: How often have you felt guilty after eating because of the effect on your shape and weight?  (Do not count binges – times when you have eaten a really big amount of food and felt out of control) |  |  |  |  |  |  |  |
| Dissatisfaction with weight | Over the past 2 weeks/14 days: How unhappy have you felt about your weight? |  |  |  |  |  |  |  |
| Discomfort seeing body | Over the past 2 weeks/14 days How uncomfortable have you felt seeing your body: for  example, in the mirror, in shop windows, when you undress  or when you have a bath or shower? |  |  |  |  |  |  |  |

